## Abstract

**Background:**

HIV-infected people who use drugs (PWUD) exhibit the highest rates of non-adherence to antiretroviral therapy (ART) among people living with HIV. This contributes to poor treatment outcomes, increased morbidity and mortality, and HIV transmission. However, current interventions fail to address the unique barriers to adherence faced by this population. Life Steps is a brief, single session intervention that demonstrated increased ART adherence among HIV-infected individuals. This study protocol seeks to improve clinical practice by adapting Life Steps for HIV-infected PWUD and adding a brief motivational intervention addressing drug use. This intervention will incorporate educational, motivational, and behavioral skills components specifically aimed at improving adherence and linkage to substance use treatment among HIV-infected PWUD.

**Methods:**

This project will consist of three phases using a mixed-methods approach. *In Phase 1*, qualitative interviews with HIV-infected PWUD and community providers, coupled with feedback from an expert review panel, will be used to enhance the existing Life Steps manual and interventionist training protocol. *In Phase 2*, the prototype will be pilot tested and qualitative exit interviews with HPWUD will identify the strengths and limitations of the intervention. Data regarding feasibility, acceptability, and barriers to delivery will guide modifications to finalize a modified Life Steps-Drug Use (LS-DU) protocol. *In Phase 3*, a pilot type 1 hybrid effectiveness-implementation trial will examine the effectiveness of LS-DU relative to a health education intervention control condition on ART adherence and viral load data at 1-, 3-, and 6-months. Data regarding clinic readiness for implementation and intervention sustainability potential will be collected.

**Discussion:**

This protocol will adapt and evaluate an intervention to improve adherence among HIV-infected PWUD. Results of this study will provide significant data on the acceptability, initial effectiveness, and sustainability potential of an adherence intervention for a high risk and underserved population.

*Trial registration* NCT02907697

## Background

Illicit drug use remains a common and significant problem among people living with HIV (PLWH). Drug use is one of the most significant barriers to antiretroviral therapy (ART) adherence, contributing to suboptimal treatment outcomes and increased transmission of HIV. As suggested by the syndemics model [1], multiple morbidities such as drug use and HIV act synergistically to produce poorer health outcomes. Over 81% of persons living with HIV report a history of illicit drug use and nearly one in four meet diagnostic criteria for a severe substance use disorder [2]. Drug use remains prevalent among PLWH enrolled in primary care with one study showing that 24% report marijuana use, 9% report amphetamine use, 8.5% report crack cocaine use, 10% report polydrug use, and almost 3% report injection drug use in the preceding 3 months [3]. This study was conducted using the CFAR Network of Integrated Clinical Systems (CNICS) data which consisted of academically affiliated HIV clinics; thus, it is possible that these are underestimates of active illicit drug use. These data demonstrate that sustainable interventions and risk reduction programs addressing substance use are needed within the HIV clinical setting.

People who use drugs (PWUD) experience unique challenges with HIV treatment and adherence. HIV-infected PWUD are more likely to experience delayed treatment, suboptimal service utilization, increased rates of HIV transmission in the community, and inferior treatment outcomes [4–6]. Relative to PLWH who do not use drugs, HIV-infected PWUD are more than twice as likely to be non-adherent to ART [7]. Both interpersonal and social factors limit adherence in this population: HIV-infected PWUD are less likely to have primary care providers or strong patient-provider relationships and have lower levels of social support [7, 8]. Socioeconomic factors prevalent in PLWH, including lack of stable housing and medical insurance, poor education and low literacy, and low health literacy pose further barriers to adherence. HIV-infected PWUD are also more likely to have medical (e.g., hepatitis C, tuberculosis) and psychiatric (e.g., depression, anxiety) comorbidity, neurocognitive impairment, and increased risk for drug overdose, which contribute to reduced adherence and poorer health outcomes [8].

### Prior adherence interventions for HIV-infected people who use drugs

Several intensive treatment approaches have been shown to improve adherence among HIV-infected PWUD including the integration of HIV care and intensive drug use treatment, directly administered ART doses at the clinic, contingency management, and peer-driven interventions [6]. Although these interventions are effective in the short-term, adherence improvements are frequently not maintained after the direct observation has been terminated [9] and such intensive interventions may not be feasible or sustainable in clinics with limited resources, which dampens the potential for widespread implementation [10]. Additionally, these interventions do not teach HIV-infected PWUD the behavioral skills needed to maintain adherence once it is achieved. Behavioral interventions overcome these limitations by teaching adherence and problem-solving skills, using brief motivational interviewing (BMI) and cognitive behavioral approaches to sustain behavior change. These interventions have been successfully augmented with booster sessions and delivered by trained clinic nurses and staff. This approach has shown promise in promoting ART adherence and self-efficacy to adhere among PLWH, but evidence is severely limited by use of small sample pilot and case studies. To date, only one behavioral adherence intervention—the Life Steps intervention—has been evaluated in HIV-infected PWUD.

Life Steps was developed by Safren and colleagues using motivational interviewing and cognitive behavioral techniques to teach the following: facts about ART and HIV, problem-solving around transportation to clinic appointments and obtaining medications, skills to improve communication with healthcare providers, strategies to cope with side effects, development of a daily medication schedule, storage of medications away from home, reminder cues for pill-taking, and responding to slips in adherence. This model consists of a brief, single session intervention that has been evaluated as both a stand-alone intervention and an adjunct to more intensive cognitive behavioral therapy (CBT). Data from multiple studies indicates that Life Steps and similar interventions are associated with increased adherence relative to self-monitoring in PLWH [7], though meta-analyses suggest that these effects are modest across studies [11, 12].

### Limitations of life steps with HIV-infected people who use drugs

Prior research on the Life Steps protocol with HIV-infected PWUD is subject to several limitations. First, only one study to date has evaluated Life Steps among a drug using population and this study focused on depressed injection drug users who are unlikely to be representative of the full range of HIV-infected PWUD [13]. Additionally, both study conditions received Life Steps; the experimental condition also received CBT for Adherence and Depression which consisted of seven CBT-focused modules. Second, no prior studies have examined which specific components of the Information-Motivation-Behavioral Model are likely to be most relevant for HIV-infected PWUD and if additional skills modules related to illicit drug use should be incorporated. Third, the Life Steps protocol focuses on skills acquisition and behavior modification related to HIV medication taking behavior, but does not address substance use or linkage to addiction treatment. Brief motivational interventions (BMIs) are especially well suited to this population, as both adherence to HIV treatment and drug use have been related to patient motivation for change [14]. Finally, there has been virtually no research examining barriers and facilitators of the implementation of behavioral ART adherence interventions within real-world clinics. Such research is essential in order to accelerate the translation of research into practice and improve the outcomes of this hard to reach, high risk population.

### Protocol objective and specific aims

The overarching objective of the current protocol is to adapt a behavioral adherence intervention for HIV-infected PWUD and obtain data on its preliminary effectiveness and implementation potential. The proposed project consists of three phases (see Table 1). *In Phase 1*, qualitative interviews with HIV-infected PWUD and community providers, coupled with feedback from an expert review panel, will be used to adapt the existing Life Steps manual and community clinician training protocol. *In Phase 2*, qualitative data from phase 1 will inform development of the intervention manual. The protocol will be pilot tested and in-depth qualitative interviews with HIV-infected PWUD and community clinicians will be used to make final refinements to the adapted Life Steps-Drug Use (LS-DU) model. *In Phase 3*, a pilot type 1 hybrid effectiveness-implementation trial will examine the effectiveness of LS-DU relative to a health education control condition on ART adherence and viral load data at 1-, 3-, and 6-months. Data regarding clinic readiness for implementation and intervention sustainability potential will be also be collected. Combined, these three phases will address three study aims:

**Table 1 Tab1:**
[figure not shown]
Clinical trial schedule of enrollment, interventions, and assessments

***Aim 1***: To adapt the Life Steps intervention by incorporating a BMI focused on linkage to substance use treatment, and tailoring the skills to meet the unique needs of HIV-infected PWUD. ***Aim 2***: To standardize the adapted intervention into a manual and train community-based intervention facilitators. ***Aim 3***: To obtain data on the preliminary effectiveness and implementation potential of the adapted intervention relative to a health education control.

## Methods

### Participants

A total of up to 84 patients and 35 clinicians will participate across three phases: 6 patients and 29 clinicians participated in Phase 1 (qualitative interviews), 18 patients and 6 clinicians will be recruited in Phase 2 (pilot testing), and 60 patients will be recruited in Phase 3 (pilot randomized hybrid trial). The primary objective for Phase 3 will be to determine a reasonable effect size for LS-DU rather than to determine statistical significance between groups. With 30 participants per group and effect size range of d = .40 to .60, power to detect the difference ranges from .54 to .75. With N = 60 we will have .80 power to detect effect sizes in the medium-large range above d = .65. Effect size estimates will include odds ratios for ART adherence and squared semi partial correlations for repeated continuous measures of putative mechanisms.

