### Phase 3 procedures: type 1 hybrid effectiveness-implementation pilot trial

#### Overview

Following the open trial, a pilot type 1 hybrid randomized effectiveness-implementation trial will be conducted to determine the effectiveness of the LS-DU protocol relative to health education. Hybrid effectiveness-implementation trials are designs that simultaneously gather data on treatment effectiveness and implementation outcomes [19]. In a type 1 hybrid trial, the primary emphasis is on the evaluation of treatment effectiveness, and the secondary emphasis is on the collection of data on implementation outcomes. Because the current study is designed to collect pilot data for a future study, measures of acceptability and feasibility are defined as the primary outcomes. Measures of effectiveness are then defined as the secondary outcomes, while data on implementation effectiveness are gathered as an exploratory outcome.

All participants will complete a baseline assessment consisting of a series of self-report measures and a urine toxicology screen. Following completion of the baseline assessment, participants will begin 2 weeks of baseline ART adherence data collection using an electronic pill cap monitoring system (MEMScaps). Only after completing the MEMS data collection will patients be randomly assigned to treatment condition using urn randomization [20] controlling for gender and viral load.

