##### Effectiveness

We will measure treatment effectiveness via adherence to HIV medication (MEMScaps), viral load (eligibility screener vs. baseline vs. 6-months), and days of drug use (Timeline Followback). Separate Generalized Estimating Equation (GEE) models for adherence will be generated for proportion of days on which study medication was taken (as indicated by MEMScap) and the proportion of expected pills taken at the 1-, 3-, and 6-month follow-ups. Examining interactions between intervention and time will test differences in adherence over the course of the intervention across the intervention conditions. As our sample size limits our ability to conduct sophisticated longitudinal analyses, we will use GEE with caution and will revert to more standard general linear models should we encounter model convergence problems. Additional measures of treatment effectiveness, including self-reported adherence, viral load, and drug use, will also be analyzed using GEE.

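### The three Phase 3 power figures for 30 per group cannot all hold under one significance level; .54 at d = .40 does not fit the other two

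*Protocol article*

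**What the plan says.** The Participants section of the protocol article sets Phase 3 at 60 patients, 30 per group. It opens with the purpose: "The primary objective for Phase 3 will be to determine a reasonable effect size for LS-DU rather than to determine statistical significance between groups". It then gives two sentences on sensitivity. The first reports, for 30 per group, "effect size range of d = .40 to .60, power to detect the difference ranges from .54 to .75". The second says: "With N = 60 we will have .80 power to detect effect sizes in the medium-large range above d = .65".

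Taken together, this is power of .54 at d = .40, .75 at d = .60 and .80 at d = .65. The article attaches no significance level, sidedness, test or correlation to these figures.

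The Effectiveness section plans GEE models of adherence at the 1-, 3- and 6-month follow-ups. It says: "Examining interactions between intervention and time will test differences in adherence over the course of the intervention across the intervention conditions". Nothing links the power figures to that model.

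**The concern.** With the number per group fixed, the power of a two-group comparison depends only on d and the significance level. Three pairs of d and power quoted for the same 30 per group must therefore lie on one curve. If they do not, at least one is misprinted or was computed on a different basis.

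These two sentences are the only quantitative account in the article of what 60 patients can show. The closing part of the Discussion says the work will inform a larger multi-site study, so the planners of that study may rely on them. A reader who applies the usual two-sided .05 would also take d = .65 as the effect detectable with .80 power, when on that basis it is not.

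**Working it through.** **Inputs.** From the Participants section: n = 30 per group; d = .40, .60 and .65; stated power .54, .75 and .80. Significance level and sidedness are not stated, so both common choices are tried.

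**Formula.** Two-sample t-test with df = 2 × 30 − 2 = 58 and noncentrality d × √(30/2) = 3.873 × d. Power is the probability that a noncentral t variable with that noncentrality exceeds the critical value (for a two-sided test, plus the negligible opposite tail). The noncentralities are:

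- d = .40: 1.549
- d = .60: 2.324
- d = .65: 2.517

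**Attempt to reproduce the stated figures.** The critical value is 1.672 for one-sided .05 (equal to two-sided .10) and 2.002 for two-sided .05.

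| d | Stated | One-sided .05 | Two-sided .05 |
|---|---|---|---|
| .40 | .54 | .455 | .332 |
| .60 | .75 | .743 | .628 |
| .65 | .80 | .800 | .697 |
| d for .80 power | .65 | .650 | .736 |

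The normal approximation gives .462, .751 and .809 one-sided, and .341, .642 and .711 two-sided. The pattern is the same. The printed .75 is closer to the normal approximation (.751) than to the t value (.743); either is within a point.

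One-sided .05 therefore accounts for .75 and .80 but not for .54. The gap at d = .40 is .54 − .455 = .085, or .54 − .462 = .078 by the normal approximation.

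**Is there another significance level that gives all three?** Solving for the one-sided level that each stated figure needs at 30 per group:

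- .54 at d = .40 needs about .076
- .75 at d = .60 needs about .052
- .80 at d = .65 needs about .050

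The last two agree within rounding; the first does not. At .076 the power would be .81 at d = .60 and .86 at d = .65, which contradicts the other two figures.

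**Does a different effect size or group size explain .54?** At one-sided .05, power of .54 needs d of about .456, or 39 per group instead of 30.

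**Does a precision gain from baseline adjustment explain the set?** At two-sided .05, the share of outcome variance that a baseline covariate would have to explain is .45 for the first figure, .25 for the second and .22 for the third. One covariate cannot have three values. At one-sided .05 the shares are .23, .02 and about 0, which again isolates the first figure. Averaging the three follow-ups fails in the same way: at two-sided .05 the implied within-patient correlation is .32, .63 and .67.

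**The case against.** **The consequence is largely disclaimed.** The Participants section puts effect-size estimation ahead of significance. The Quantitative data analysis plan expects few null hypotheses to be rejected. The Hypotheses testing section looks for a supportive pattern, with feasibility and acceptability as the primary outcomes, and the Discussion lists the small sample as a limitation. This stands: no design decision or primary analysis turns on the power figures, and that is why the point is minor.

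**An unstated significance level is not in itself a fault in a journal article**, since the full protocol or analysis plan may give it. This also stands. The fault is that the printed figures disagree with one another whatever the level is.

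**A reader might infer that the true power is .33 to .63 and that the trial is far less sensitive than presented.** The documents do not support this. Those values hold only under two-sided .05, which the article does not state. Two of the three figures match one-sided .05, or equally two-sided .10, and the secondary hypothesis in the Hypotheses testing section is directional. On that basis d = .65 for .80 power is correct and only the lower end is overstated.

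**A reader might also infer that losses make the figures worse.** Randomisation comes after the 2-week adherence monitoring ("Only after completing the MEMS data collection will patients be randomly assigned to treatment condition"), and follow-up lasts 6 months. But the first power sentence is conditional on 30 per group, and patients belong to a group only once randomised. The article gives no loss rate, and GEE can use data from patients with incomplete follow-up. Any figure for lost power would rest on an invented rate.

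**Conclusion.** Wrong as written, with minor consequence. At 30 per group, no single significance level and sidedness yields .54, .75 and .80 at d = .40, .60 and .65.

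The most likely basis is one-sided .05 (equal to two-sided .10), because it reproduces two of the three. That is an inference, since the article does not say so. On that basis one figure is wrong: .54 should be about .45 to .46, an overstatement of 8 to 9 points. If two-sided .05 was meant, all three are too high, by about 21 points at d = .40 (.54 against .33), 12 at d = .60 (.75 against .63) and 10 at d = .65 (.80 against .70), and .80 power needs d of about .74 instead of .65.

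The calculation assumes a two-sample comparison of means with 30 analysed in each group. The failure of the three figures to agree does not depend on which significance level is chosen.

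**What to change.** State the test, significance level and sidedness behind the two power sentences, and restate the figures to match:

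- If the basis is one-sided .05 or two-sided .10, say so, change .54 to about .46, and keep .75 and d = .65.
- If the basis is two-sided .05, replace the range with .33 to .63 for d = .40 to .60, and give d = .74 as the effect detectable with .80 power.

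The cost is an edit to two sentences. The stated sensitivity becomes less favourable, slightly in the first case and more clearly in the second. The sample size, conduct and planned analyses do not change.

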##### Hypotheses testing

Given the developmental nature of this study, our primary goal is to establish feasibility and acceptability of the LS-DU and assessment procedures to be implemented in a future larger scale hybrid type 2 randomized trial. Our primary hypothesis is that participants completing and community clinicians delivering the LS-DU intervention will report high levels of acceptability of the intervention. Our secondary hypothesis is that the LS-DU intervention will demonstrate greater effectiveness than the health education outcome in terms of promoting days of adherence to HIV medication and reducing substance use. We will also collect exploratory data on implementation potential of the intervention and moderators of implementation effectiveness. Due to the small sample size, we will primarily be hoping to find a pattern of results that is supportive of the LS-DU rather than rigorously testing hypotheses to determine a stable effect size.

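### For the putative-mechanism measures, the named effect size (squared semi-partial correlation) has no sign and is biased upward at N = 60; a signed estimate with an interval should replace or accompany it

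*Protocol article*

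**What the plan says.** The Participants section sets the purpose of Phase 3: "The primary objective for Phase 3 will be to determine a reasonable effect size for LS-DU rather than to determine statistical significance between groups". It plans on the standardised mean difference scale: "With 30 participants per group and effect size range of d = .40 to .60, power to detect the difference ranges from .54 to .75", and "With N = 60 we will have .80 power to detect effect sizes in the medium-large range above d = .65". It then names the effect sizes to be reported: "Effect size estimates will include odds ratios for ART adherence and squared semi partial correlations for repeated continuous measures of putative mechanisms". Adherence thus gets an odds ratio and the repeated continuous mechanism measures get a squared semi-partial correlation. No signed measure, bias-adjusted version or interval is named for the mechanisms.

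The Effectiveness section ties models to outcomes. For adherence: "Separate Generalized Estimating Equation (GEE) models for adherence will be generated for proportion of days on which study medication was taken", and likewise for the proportion of expected pills taken. For the rest: "Additional measures of treatment effectiveness, including self-reported adherence, viral load, and drug use, will also be analyzed using GEE". The fallback is stated as "we will use GEE with caution and will revert to more standard general linear models should we encounter model convergence problems". No mechanism measure is named in that section.

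The article does not list the putative mechanisms. Table 3 has repeated exploratory measures such as HIV treatment self-efficacy and depression, which the Assessments text calls potential moderators. I take measures of this kind as the likely candidates; that is an assumption.

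**The concern.** For a mechanism measure, the first question is direction. An intervention meant to build skills and motivation should raise self-efficacy and, if anything, lower depression. A squared semi-partial correlation says how much outcome variance goes with treatment arm, but not which arm did better. Its sampling distribution also starts at zero, so its mean lies above zero even when treatment does nothing.

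At stake is how the mechanism results are read. A table of these values alone would show a positive number for every mechanism, including those that did not move and those that moved the wrong way. The values would also be on a different scale from the d used for planning, and could be converted only to an absolute d carrying the same upward bias.

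**Working it through.** The plan gives no figure for this metric, so there is none to reproduce. The power values in the same paragraph show only the planning scale and are not used below.

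**Inputs.** 30 per arm, N = 60 (Participants section). Values of d from 0 to .60, where .40 to .60 is the plan's range and 0 and .20 are added to show small effects. Normal outcome with SD 1. First case: one visit, no covariate, so the semi-partial correlation is the ordinary correlation r between arm and outcome.

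**Formulas.**
- True value with equal arms: r² = (d²/4)/(1 + d²/4). At d = ±.40 this is .04/1.04 = .0385.
- Mean under no effect, one treatment term: 1/(N - 1) = 1/59 = .0169.
- Conversion in the no-covariate case: |d| = 2·√(r²/(1 - r²)). For .0169 this is 2·√(.0169/.9831) = .26.
- Bias-adjusted version: 1 - (1 - r²)·59/58.

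**Simulated means** (50,000 trials per row, one visit, no covariate):

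| True d | True r² | Mean r² | Mean adjusted r² |
|---|---|---|---|
| -.40 | .0385 | .0540 | .0377 |
| 0 | 0 | .0166 | -.0003 |
| +.20 | .0099 | .0263 | .0095 |
| +.40 | .0385 | .0542 | .0379 |
| +.60 | .0826 | .0971 | .0815 |

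Three things follow.
1. The rows for -.40 and +.40 agree apart from simulation error: the metric does not tell benefit from harm.
2. The bias is roughly constant at .015 to .017, so it matters most for small effects. The mean is .0263/.0099 = 2.7 times the true value at d = .20, .0542/.0385 = 1.4 times at d = .40, and .0971/.0826 = 1.2 times at d = .60.
3. The adjustment removes nearly all the bias but does not restore the sign.

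**Sensitivity to assumptions not in the article.**
- One baseline covariate, correlation .5 with the outcome (10,000 trials): mean .013 under no effect, and .050 at both d = +.40 and d = -.40, against a true .0385.
- Three visits pooled, intraclass correlation .5 (8,000 trials): mean .011 under no effect and .049 at d = .40. The value depends on how within-person variance enters the denominator, which the article does not say.
- 48 analysed instead of 60, one visit, no covariate: 1/47 = .021 under no effect.

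The bias changes in size across these settings but persists in each.

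**Model.** A squared semi-partial correlation is the drop in explained sum of squares when a term leaves a least-squares model. GEE, the main longitudinal method named, does not give it as standard output. The general linear model named as fallback does. The article assigns neither to the mechanism measures.

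**The case against.** The best defence is that this is a modest descriptive metric for a side question in a pilot. Much of that stands.

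- **Scope.** A reader might infer that all continuous effectiveness outcomes will be summarised this way. The documents do not support that. The sentence limits the metric to putative mechanisms, adherence gets an odds ratio, which has a direction, and viral load and drug use are not assigned the metric anywhere.
- **GEE.** A reader might infer that the metric conflicts with the planned analysis. It does not: GEE is planned for effectiveness outcomes, and the fallback model does supply the metric. What remains is that no model is tied to it.
- **Hidden harm.** The list of effect sizes is open, and any fitted model gives signed coefficients and group means. Direction is lost only if the squared value is reported alone. The article does not say it will be, but it commits to no signed measure for the mechanisms either.
- **Judging LS-DU and sizing the next trial.** The Hypotheses testing section says "we will primarily be hoping to find a pattern of results that is supportive of the LS-DU", but this follows a secondary hypothesis about adherence and substance use, not mechanisms. The same section disclaims a stable effect size. Nothing says a mechanism's squared correlation will size the larger trial, so a consequence for its sample size cannot be claimed.
- **Size.** The bias is under .02 of variance and easily adjusted. Taking a square root to convert it to d makes a value near zero look larger. That is fair, but d is the article's own planning scale, and at d = .20 the bias exceeds the true value.

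**Conclusion.** The point holds for the repeated continuous mechanism measures and no further. The named metric is unsigned by construction and biased upward at N = 60. Its mean under no effect is about .017 (|d| about .26) with one visit and no covariate, or about .011 to .013 in the two other N = 60 settings tried. At d = .40 in either direction it averages about .054 against .038. These figures assume normal outcomes and all 60 participants analysed; the lack of sign needs no assumption. The absence of a stated model adds ambiguity about what the value would mean over repeated visits.

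The choice is a poor fit with an estimation objective, not an error that invalidates the trial. It leaves the feasibility, acceptability and effectiveness outcomes untouched. It is worth changing because a better summary comes from the same data at almost no cost.

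**What to change.** In the Participants section, replace the squared semi-partial correlation with, or report beside it, the signed adjusted LS-DU minus control difference from the fitted model for each mechanism measure. Give it raw and standardised, on the d scale used for planning, with a 95% confidence interval. Name the model it comes from. If the squared semi-partial correlation is kept, use a bias-adjusted version.

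The cost is one sentence and no new data. The downside is that intervals will visibly include zero and negative values. With 30 per arm and no covariate, the half-width on the d scale is about 1.96·√(2/30) = .51, so an observed d of .40 would carry an interval from about -.11 to .91. That is an honest picture of what 60 participants can show.
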